## Abstract

**Background:**

The diagnosis of Pulmonary Embolism (PE) in the emergency department (ED) is crucial. As emergency physicians fear missing this potential life-threatening condition, PE tends to be over-investigated, exposing patients to unnecessary risks and uncertain benefit in terms of outcome. The Pulmonary Embolism Rule-out Criteria (PERC) is an eight-item block of clinical criteria that can identify patients who can safely be discharged from the ED without further investigation for PE. The endorsement of this rule could markedly reduce the number of irradiative imaging studies, ED length of stay, and rate of adverse events resulting from both diagnostic and therapeutic interventions. Several retrospective and prospective studies have shown the safety and benefits of the PERC rule for PE diagnosis in low-risk patients, but the validity of this rule is still controversial. We hypothesize that in European patients with a low gestalt clinical probability and who are PERC-negative, PE can be safely ruled out and the patient discharged without further testing.

**Methods/Design:**

This is a controlled, cluster randomized trial, in 15 centers in France. Each center will be randomized for the sequence of intervention periods: a 6-month intervention period (PERC-based strategy) followed by a 6-month control period (usual care), or in reverse order, with 2 months of “wash-out” between the 2 periods. Adult patients presenting to the ED with a suspicion of PE and a low pre test probability estimated by clinical gestalt will be eligible. The primary outcome is the percentage of failure resulting from the diagnostic strategy, defined as diagnosed venous thromboembolic events at 3-month follow-up, among patients for whom PE has been initially ruled out.

**Discussion:**

The PERC rule has the potential to decrease the number of irradiative imaging studies in the ED, and is reported to be safe. However, no randomized study has ever validated the safety of PERC. Furthermore, some studies have challenged the safety of a PERC-based strategy to rule-out PE, especially in Europe where the prevalence of PE diagnosed in the ED is high. The PROPER study should provide high-quality evidence to settle this issue. If it confirms the safety of the PERC rule, physicians will be able to reduce the number of investigations, associated subsequent adverse events, costs, and ED length of stay for patients with a low clinical probability of PE.

**Trial registration:**

NCT02375919.

## Background

### Pulmonary embolism in the emergency department

The incidence of pulmonary embolism (PE) in France and Europe has been estimated to 0.6–0.9 per 1000 persons per year [1, 2]. PE is a potentially lethal diagnosis [3], and its diagnosis in the Emergency Department (ED) is challenging [4].

The fear of missing this diagnosis and the poor specificity of its clinical presentation has led physicians to suspect PE in patients who present with a broad variety of symptoms such as dyspnea, chest pain, syncope, and hypotension. These patients account for more than 10 millions ED visits a year in the United States. For the last decade, the strategy for PE diagnosis has been well-defined (Fig. 1). The usual work-up for PE diagnosis first includes an assessment of the clinical probability of PE, using a structured score (the Revised Geneva Score (RGS) or Wells’ score [5, 6]), or an unstructured estimation of the clinical probability (referred to as the clinician “gestalt” [7–9]). In patients with low clinical probability to moderate clinical probability, sensitive D-dimer testing should be followed if positive by a Computed Tomography Pulmonary Angiogram (CTPA) in the absence of contra-indication. Patients with a high clinical probability should undergo CTPA without the need for preliminary testing. This diagnostic strategy is recommended by European guidelines [10], national expert recommendations [11] and local policies. It has been validated and is safe to exclude PE in outpatients visiting the ED [12]. However, due to its low specificity (40–60 %) [9, 13], D-dimer testing may lead to more than 50 % of false positives and subsequent CTPA [9]. Furthermore, the wide availability of D-dimer testing, combined with the fear of missing PE, has led to lowering the testing threshold for suspicion of PE; hence the decrease in the prevalence of confirmed PE from 30 % to below 10 % in the United States [14–17].

**Fig. 1 Fig1:**
[figure not shown]
Standard strategy for the diagnosis of pulmonary embolism (PE) in the Emergency Department (ED). ED, Emergency Department; PE, pulmonary embolism; RGS, Revised Geneva Score

Subsequently, there has been a marked rise (up to 15-fold) in the utilization of CTPA in the last 15 years [18] and in the incidence of diagnosed PE [19]. However, this greater incidence of PE was not followed by a decrease in the mortality rate from PE, but rather a global decrease in PE fatality [19, 20]: the prognosis of a patient with a PE improves, but the overall number of deaths from PE do not change. This suggests that PE tends to be “overdiagnosed”: small PEs are more frequently diagnosed, with no clear benefit in terms of outcomes. This increased exposure to CTPA may be a source of unnecessary risks, such as contrast-induced nephropathy and allergic reactions, adverse events after anticoagulation treatment or the delayed occurrence of radiation-induced cancer [21–23].

### The PERC rule

Assessing the benefit risk ratio for PE investigation, it has been calculated (using the Pausker and Kassirer method [24]) that if the pre test probability (PTP) is below 1.8 %, patients should not undergo D-dimer testing because a positive result would mandate a CTPA, which would have a negative benefit risk ratio [15]. To reduce the rate of unnecessary testings for PE caused by overuse of D-dimer, in 2004 Kline et al. developed a block rule of 8 binary variables (PERC rule): age < 50 years, pulse < 100 bpm, arterial oxygen saturation (SpO_2_) > 94 %, no unilateral leg swelling, no hemoptysis, no recent trauma or surgery, no prior PE or deep venous thrombosis (DVT) and no exogenous estrogen use [15] – PERC-negative patients are defined as fulfilling these 8 criteria. Kline et al. applied this rule in their princeps study to low-clinical-probability patients, defined by a probability of less than 15 % by empirical clinical gestalt [15, 16]. They reported that the prevalence of PE for PERC-negative patients was 1.4 % (95 % confidence interval (CI) 0.5–3 %). This low rate suggests that PERC-negative patients could be safely discharged after clinical examination without further testing. Moreover, the rate of 1.4 % is below the reported upper limit of false-negative rates after pulmonary angiogram or CTPA (3 %) [12, 25, 26], which advocates for a safe alternative to further testing.

Following this princeps study, several other studies assessed the safety of a PERC-based policy to exclude PE in low-risk emergency patients with a PERC-negative rule. Two meta-analyses [17, 27] confirmed the benefits and safety of the PERC rule, with a rate of PE after follow-up lower than 1 % in PERC-negative patients. They included 10 prospective and 3 retrospective studies, i.e. non-interventional studies only, accounting for a total of 14,844 ED patients with a suspicion of PE. Three of the 13 studies were conducted in Europe (France, Belgium and Switzerland) [28–30]. In the first 2 European studies [28, 29] the prevalence of PE amongst PERC-negative patients was 5.4 % and 6.7 %, respectively (95 % CI 3–10 %). Their authors argued that the higher prevalence of PE in Europe (>20 % [17]) than in the United States (<10 % [17]) was the main reason for this lower negative predictive value, and that this rule should not be applied in high-prevalence populations. Based on the poor performance of the PERC rule, European physicians have been reluctant to apply it for excluding PE in low-risk patients. However, these two studies had several methodological bias: both studies were retrospective and did not collect PERC items prospectively. Moreover, the studied samples were not solely patients with a low gestalt clinical probability: they included unselected patients with suspected PE in the ED, with low PTP to high PTP. Although authors from one study ran a sensitivity analysis focusing on patients with low PTP, this was assessed using the Revised Geneva Score (RGS) that is based on redundant items with those of the PERC rule. These specific limits, coupled with the greater prevalence in the European studies, might explain the greater rate of false negatives. A few years later, Penaloza et al. reported that the PERC rule was safe even in Europe, when combined with a low clinical probability assessed by physician’s gestalt [30], with no venous thromboembolic (VTE) event after 3-month follow-up. Accordingly, in a recent multicenter retrospective study, we also observed a very low prevalence of PE (0.5 % (95 % CI 0.1–1.1 %)) amongst low-risk, PERC-negative ED patients [31].

Of note, all of the previously cited studies were either prospective or retrospective, but no randomized study has yet compared the benefit risk ratio of a PERC-based strategy versus the standard diagnostic strategy (Fig. 2) on occurrence of undiagnosed PE in low-risk patients.

**Fig. 2 Fig2:**
[figure not shown]
Work-up for diagnosis of pulmonary embolism (PE). **a** Control group. **b** Intervention group. CTPA, Computed Tomography Pulmonary Angiogram; PE, pulmonary embolism; PERC, Pulmonary Embolism Rule-out Criteria

## Methods

The PROPER trial is a cluster randomized trial in France. The primary objective of this study is to assess the non-inferiority of a PERC-based diagnostic strategy for PE low-risk emergency patients, compared to the standard strategy of D-dimer testing, on the occurrence of undiagnosed VTE events. Our institutional review board authorized the study with the need for a signed informed consent from the patient (Comité de protection des personnes, Paris Ile de France 6, A00215-44).

### Experimental plan

Each center will be randomized for the period: a 6-month intervention period followed by a 6-month control period, or a 6-month control period followed by a 6-month intervention period. The randomization will be prepared by URC-Est using permutation blocks (SAS 9.3, SAS Inc., Cary, NC, USA) before the first site initiation visit. The design, conduct and reporting of this study will follow the Consolidated Standards of Reporting Trials (CONSORT) statement extended to cluster randomized trials [32]. The two groups will have a different work-up for the diagnosis of PE in the ED as follows:Control group: standard strategy: conventional PE work-up. Every low-risk patient will undergo sensitive D-dimer testing, with subsequent CTPA if positive. In case of negative D-dimer, PE will be considered as excluded (Fig. 2a).Intervention group (PERC-based strategy): PE work-up based on the use of the PERC rule. If all PERC criteria are negative, no further testing for PE will be recommended. If at least one criterion is positive, then the patient will undergo sensitive D-dimer testing, with subsequent CTPA if positive. In case of negative D-dimer result, PE will be considered as excluded (Fig. 2b).

It has been recently reported that the cut-off for positive D-dimer should be changed for patients aged > 50 years to age × 10 ng/ml [33]. This strategy has been validated in a large multicenter international trial [34]. This strategy is actually endorsed by our centers. The strategy for defining “positive D-dimer” (age × 10 ng/ml for patients older than 50 years) will be stated before the start of the study in each center and not changed during the whole study period. Of note, this change will only concern patients aged 50 years or greater, i.e. with a PERC > 0. As this will not affect PERC-negative patients, there will be no interference with our objectives.

### Selection of participants

All patients with chest pain or dyspnea who attend one of the participating centers will be screened for eligibility by ED physicians and research assistants. If the treating ED physician or local investigator considers that the patient has a sufficient clinical suspicion of PE and that he needs a formal work-up for this diagnosis, and that this suspicion is low enough to discard this suspicion in case of negative D-dimer (i.e. estimated as less than 15 %), then the patient will be eligible. When a patient is eligible, his written informed consent will be obtained. In case of inability to consent, the patient will not be included in the study. The inclusion criteria are as follows:Patients ≥ 18 years presenting to an ED ANDNew onset of, or worsening of shortness of breath or chest pain ANDA low clinical probability of PE, estimated by the clinician gestalt (unstructured empirical probability of PE) to be lower than 15 %

Exclusion criteria include the presence of any obvious cause other than a PE of symptoms, an acute severe presentation (clinical signs of respiratory distress, hypotension, SpO2 < 90 %, shock), a contraindication to CTPA (allergy, or estimated creatinine clearance less than 30 ml/min), pregnancy, concurrent anticoagulation treatment, current diagnosis of VTE event, inability to follow-up or to provide informed consent, lack of coverage for medical insurance, being a prisoner, and participation in another intervention trial.

After a patient is screened in the ED and may be included, the patient’s emergency physician, the local investigator or a clinical research technician (CRT) will inform them of the trial, and obtain signed informed consent. After a patient is included in the study, the local investigator, the patient’s emergency physicians, or the CRT will collect data on their past medical history, vital signs on admission, PERC, RGS, Wells’ score, examination in the ED and discharge disposition. This will be collected on a paper Case Report Form (CRF), later entered on an electronic CRF (eCRF). Any missing data will be sought through electronic or paper records of the patients, under the supervision of the local investigator of the center.

### Trial objectives and outcomes

The primary objective of this study is to assess the non-inferiority of a PERC-based diagnostic strategy for ED patients with a low probability of PE based on physician’s gestalt, compared to the standard strategy of D-dimer testing, on the prevalence of undiagnosed VTE events. The secondary objectives are the following:to assess the reduction of unnecessary irradiative imaging studies and adverse eventsto assess the reduction in ED length of stayto assess the reduction of onset of anticoagulation regimen and associated adverse eventsto assess the reduction of hospital admission following the ED visit, hospital readmission, and mortality at 3 months.

The primary outcome is the percentage of diagnostic strategy failure, defined as diagnosed VTE at 3-month follow-up, among patients for whom PE has been initially ruled-out. Exclusion of PE in the ED is made based upon a negative D-dimer result or a negative CTPA in both groups, or a negative PERC in the intervention group.

Follow-up will be made by telephone interview of the patient or his general practitioner, and review of any outpatient consultation or hospital visit at 3 months (13 weeks) by a CRT. The time frame of the 3-month follow-up period could be subject to minor adjustments, but should occur between day 84 and day 98. Follow-up visit or interview will seek the occurrence of VTE events (DVT documented with ultrasonography of the lower limbs or venous computed tomography (CT), or PE documented with positive CTPA or high probability ventilation/perfusion (V/Q) lung scan), death, return visit to the ED, and hospitalization. All medical records pertaining to the patient within this timeframe will be sought and analyzed by the local investigator, looking for reports of VTE events, or adverse events from CTPA or anticoagulation. In case of death, report of a VTE, or major cardiovascular event, the file will be analyzed by a committee of three independent experts. This method of adjudication has been described and validated in all major previous PE diagnostic studies [35, 36].

The primary criterion of a VTE event will be based on an objective diagnosis of DVT on Doppler ultrasonography, an intraluminal defect on CTPA, or a V/Q lung scan with a reported high probability. To confirm the occurrence of the primary endpoint, all files with evidence of a thromboembolic event collected by the local investigator of each center will be independently reviewed by an adjudication committee of three experts, blinded one to the other, and blinded to the study group. The adjudication committee will also review cases of death with no evidence of VTE event and will adjudicate whether or not the death is likely related to a PE. A sudden death in the absence of other obvious cause will be adjudicated as related to a PE. This committee will include three members, independent from the trial, with expertise in the field of PE, and will meet the recommendations of Dechartres et al. [37].

The result of adjudication regarding the primary endpoint, and other secondary endpoints at follow-up will be entered on the eCRF by a CRT or the local investigator.

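### Blinded adjudication covers only the files that sites refer, and for non-fatal events referral rests on record review by an investigator who knows the period's strategy

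*Protocol article*

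**What the plan says.** Under Experimental plan, each center is randomized to an order of two six-month periods, one per strategy. In the control period, "Every low-risk patient will undergo sensitive D-dimer testing, with subsequent CTPA if positive". In the intervention period, a patient negative on all PERC items is recommended no further testing.

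Under Trial objectives and outcomes, "Follow-up will be made by telephone interview of the patient or his general practitioner", together with a review of outpatient and hospital visits by a clinical research technician. In addition, "All medical records pertaining to the patient within this timeframe will be sought and analyzed by the local investigator, looking for reports of VTE events". Blinding is stated for the adjudication committee, whose three members are "blinded one to the other, and blinded to the study group". No blinding is stated for the local investigator or the technician.

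Referral to the committee is described twice in that section:

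- The follow-up paragraph: "In case of death, report of a VTE, or major cardiovascular event, the file will be analyzed by a committee of three independent experts".
- The next paragraph, which covers endpoint confirmation: "all files with evidence of a thromboembolic event collected by the local investigator of each center will be independently reviewed by an adjudication committee". It adds: "The adjudication committee will also review cases of death with no evidence of VTE event".

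The VTE criterion is "based on an objective diagnosis of DVT on Doppler ultrasonography, an intraluminal defect on CTPA, or a V/Q lung scan with a reported high probability". The article does not say what a committee file contains.

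**The concern.** Blinded adjudication protects how a referred file is classified. It does not protect the step before, at which someone decides that a record contains evidence of VTE. Here that step is taken at the site, where the strategy in force is known. The correction runs one way: the committee can strike out a false event but never sees a missed one. The article describes no independent check of files that were not referred.

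If fewer events were recognised in the PERC periods than in the control periods, the observed difference would shrink. In a non-inferiority trial that favours the hypothesis under test. The endpoint is rare, so a small differential loss could matter.

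Two related points are less certain. The two referral lists are not the same, so 15 sites could apply different ones. And an index record that shows a PERC-negative patient without a D-dimer would point to the intervention arm, which could undo the stated blinding of the committee.

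**Working it through.** **The plan's own figures.** From Statistical analysis and the sample size section: control rate 1.5%, margin 1.5 points, one-sided alpha 5%, power 80%, decision by the upper bound of the two-sided 90% interval.

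- Per arm: (1.645 + 0.842)² × 2 × 0.015 × 0.985 / 0.015² = 812, so 1,624 in all, as stated.
- Design effect: 1 + (60 − 1) × 0.002 = 1.118, as stated.
- 1,624 × 1.118 / 30 = 60.5, rounded up to 61 per cluster. With 5% added this is about 64, and 64 × 30 = 1,920, as stated.

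These figures are not in dispute. They set the scale for what follows.

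**Events at stake.** 0.015 × 812 = 12.2 events in an arm at 1.5%, and 0.03 × 812 = 24.4 at 3.0%. One event moves the difference by 100 / 812 = 0.12 points.

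**Where the decision turns.** Upper bound = (pT − pC) + 1.645 × √{[pC(1 − pC) + pT(1 − pT)] / 812}, with 12 control events (pC = 1.478%):

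- 15 intervention events: difference 0.369 points, standard error 0.635, upper bound 1.41%. Non-inferior.
- 16 intervention events: difference 0.493 points, standard error 0.646, upper bound 1.56%. Not shown.

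At 912 per arm (1,920 × 0.95 / 2) with 14 control events, 18 pass (1.45%) and 19 fail (1.575%).

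**Effect of unequal referral.** True rates are set at 3.0% and 1.5%, the edge of the margin. A share f of intervention events alone is not referred, so the observable rate is 3.0% × (1 − f). The table gives the probability of declaring non-inferiority, by exact binomial enumeration of the rule above without clustering. The document gives no value of f; the range is assumed.

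| f | Observable rate | Events lost on average (812 per arm) | False non-inferiority, 812 per arm | 912 per arm |
|---|---|---|---|---|
| 0 | 3.00% | 0 | 5.6% | 5.6% |
| 5% | 2.85% | 1.2 | 8.4% | 8.5% |
| 10% | 2.70% | 2.4 | 12.1% | 12.5% |
| 20% | 2.40% | 4.9 | 23.4% | 24.8% |

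**The two referral lists side by side.**

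| Trigger | Follow-up paragraph | Primary-endpoint paragraph |
|---|---|---|
| VTE reported or evident | yes | yes |
| Death | yes | yes |
| Major cardiovascular event | yes | not named |

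The only difference is the last row. An equivocal CTPA that the site reads as negative falls under neither list, so aligning the wording alone would not bring it to the committee.

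**Could the file reveal the arm?** PERC items are collected in both groups (Selection of participants), so a PERC result alone does not give the arm. The signal is a PERC-negative patient with no D-dimer, because every control patient is to have one. The Discussion puts PERC-negative patients at 15-30% of those with low probability. They are a minority, but the only patients whose recommended work-up differs between strategies.

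**The case against.** The strongest reply is that the endpoint is reasonably well guarded. Deaths and reported VTE go to the committee by rule, and no text lets a site withhold them. The criterion is imaging-based. Case-finding does not depend on the investigator alone, since a technician also contacts the patient or general practitioner and reviews visits. A sudden death with no other obvious cause counts as PE by a fixed rule. All of this stands. A reader might infer that blinded adjudication fails to protect the primary endpoint at all; the document does not support that.

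What the reply leaves open is that a referral rule acts only once someone has recognised evidence of VTE. Nor is that recognition fully fixed: DVT is described by leg ultrasonography or venous CT in the follow-up paragraph, by Doppler ultrasonography in the next, and by proximal compression ultrasonography under Statistical analysis.

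Three further inferences also go too far:

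- That the two lists contradict each other. The second does not call itself exclusive, and major cardiovascular events are not part of the primary endpoint. The wording differs and should be aligned; no more than that.
- That the committee is in fact unblinded. This depends on file contents that the article does not give. Masking may be set out in the full protocol or a committee charter, and the article commits the committee to a cited set of adjudication recommendations.
- That two to four lost files would reverse the expected result at the margin. At 24 versus 12 events, losing two to four leaves 22 to 20, with upper bounds of 2.40% to 2.12%, which still fail. Nine would have to be lost to reach 15. Small losses matter when the count is already near the boundary.

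One-sided under-referral is itself an assumption. Closer vigilance in the PERC periods could push the other way.

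**Conclusion.** The point holds in limited form. Protection by blinded review begins only at referral, and for non-fatal events referral depends on unblinded review at the site, so unequal recognition between periods cannot be corrected later. The difference between the two lists is real but small. Masking of the index work-up is something to confirm, not a demonstrated fault.

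The exposure is a pass/fail boundary one event wide (15 versus 16 against 12 controls) and, under an assumed 5-20% loss in the intervention arm alone, false non-inferiority of about 8-23% against 5.6% with full referral. These figures rest on 812 per arm, a simple 90% interval, no clustering, and a loss that the document neither states nor suggests has occurred. They show sensitivity, not an estimate of actual bias. The change is worth making because it is cheap and removes most of the local judgement from referral.

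**What to change.** Use one referral list in both paragraphs of Trial objectives and outcomes, based on recorded facts and not on whether the site believes VTE occurred. Send the committee every patient who, after the index visit, had any of the following:

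- death;
- any CTPA, V/Q scan, venous CT or leg ultrasound, whatever the result;
- newly started anticoagulation;
- a major cardiovascular event.

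Confirm, or state if it is not yet written anywhere, that files reach the committee with the index D-dimer and study period masked. Replace calendar dates with days since inclusion. Dates should not simply be deleted, because the committee must be able to check that an event fell within the 3-month follow-up (contact between day 84 and day 98).

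The cost is more files for the existing three-member committee and some central redaction. No new assessor, visit or procedure is needed. The number of extra files cannot be worked out from the article.
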